### **9.3 Recording of adverse events**

Non-serious AE: Only some of the non-serious AEs will be collected from time of randomization throughout the treatment/follow-up periods to the Study Closure Visit. Other non-serious AEs are up to the investigator to decide whether to collect.

SAE: All SAEs will be collected and recorded.

### **9.4 Causal relationship between adverse events and study:**

Attribution of: (1) Definite; (2) Probably; (3) Possibly; (4) Unlikely; (5) Not related; (6) Not applicable.

### **9.5 Obligation of the investigator regarding safety reporting**

#### **9.5.1 Adverse events**

All AEs will be recorded on the corresponding page(s) in the CRF. Whenever possible, symptoms should be grouped as a single syndrome or diagnosis. The Investigator should specify the date of onset, intensity, action taken with respect to the Investigational Product, corrective treatment/therapy given, outcome and his/her opinion about whether it is possible that the AE is caused by the study intervention, related to the index stroke, other cause, or intercurrent condition.

#### **9.5.2 Serious adverse event**

For SAEs, the investigator must immediately take corresponding measures:

Immediately notify the representative of the Monitoring Team, send the signed and dated corresponding pages in the CRF to the representative of the Monitoring Team,

and attach a photocopy of all examinations conducted and the examination dates. For laboratory results, include the laboratory normal ranges. The contact information (name, address and fax number) of the representative is on the Clinical Trial Protocol. These measures should be completed no later than **24 hours** after SAE.

Care should be taken to ensure that the patient's identity is protected and the patient's identifiers in the Clinical Trial are properly noted on all copies of source documents provided to the Sponsor.

### **9.5.3 Follow-up and risk management**

The Investigator should take all appropriate measures to ensure the safety of the patients.

Screening of subjects should strictly follow the inclusion and exclusion criteria of the study. If an AE occurs during the study period, relevant evaluations will be performed, including blood routine examination, coagulation, creatinine, hepatic function, renal function, arterial blood gas analysis, ultrasound and computer tomography. Targeted treatment and necessary consultation should be carried out in a timely manner. When addressing SAEs, it is important to make sure the patient's airway is clear, respiration, blood pressure and heart rate are stable.

Notably, the investigator should follow up the outcome of any AEs (clinical signs, laboratory values or other, etc.) until the patient's condition returns to normal or stabilizes. The follow-up will continue even if the patient withdraws from the clinical trial, and the patient will be interviewed by telephone or face-to-face at the scheduled visit time. The monitoring team may request additional visits and investigations.

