### **9.5.3 Follow-up and risk management**

The Investigator should take all appropriate measures to ensure the safety of the patients.

Screening of subjects should strictly follow the inclusion and exclusion criteria of the study. If an AE occurs during the study period, relevant evaluations will be performed, including blood routine examination, coagulation, creatinine, hepatic function, renal function, arterial blood gas analysis, ultrasound and computer tomography. Targeted treatment and necessary consultation should be carried out in a timely manner. When dealing with SAEs, it is important to make sure patient's airway is clear, respiration, blood pressure and heart rate is steady.

Notably, the investigator should follow up the outcome of any AEs (clinical signs, laboratory values or other, etc.) until the patient's condition returns to normal or stabilizes. The follow-up will continue even if the patient withdraws from the clinical trial, and the patient will be interviewed by telephone or face-to-face at the scheduled visit time. The monitoring team may request additional visits and investigations.

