##### **(2) Per Protocol Set (PPS)**

The PPS is a subset that includes all subjects who were treated with the treatment

assignment to which they were randomized and there are no clinically meaningful deviations from the protocol. Severe deviations from the protocol will be finally defined during the data auditing process, including but not limited to the followings:

- 1) The subject is not in line with the inclusion criteria.
- 2) There are other treatments that potentially confound the appraisal of efficacy of the planned treatment.
- 3) Poor compliance.
- 4) Follow-up interval exceeds the required time window.

Secondary analysis will be conducted on the PPS. If its result are not consistent with that of the FAS, a detailed analysis to examine the difference(s) will be required.

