## **11. Ethical standards**

### **11.1 Ethical standards**

This Clinical Trial will be conducted in accordance with the principles laid down by the 18th World Medical Assembly (Helsinki, 1964) and all applicable amendments laid down by the World Medical Assemblies and the ICH guidelines for Good Clinical Practice. Prior to initiating the study, each site will obtain Institutional review board (IRB) or institutional ethics committee (IEC) approval for the protocol, informed consent forms and materials used to recruit subjects. Before each subject is enrolled, the investigator is responsible for fully and comprehensively introducing the purpose, procedures and possible risks of the study to the subject or his/her agent, signing a written informed consent form, and informing the subjects that he has the right to withdraw from this study at any time. The informed consent should be kept as a clinical study document for future reference. The personal privacy and data confidentiality of subjects will be protected during the study process.

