## 10. Data handling conventions

### Premature Withdrawal and Missing Data

If any subject withdraws prematurely from the study (prior to the final visit D90±7 days assessment), they are required to complete the withdrawal visit in the CRF. The reasons for withdrawal will be presented in a summary table. For the purposes of summaries and analysis of clinic visit data, this visit will be assigned to the next scheduled clinic visit for that subject, regardless of whether the date falls within the next visit window.

Subjects who withdraw before the end of the study, but who do provide at least one post-baseline measure for a particular endpoint, will be included in the analysis. Subjects who do not attend any visits after randomization will be excluded from analysis of any endpoint, as no post-baseline data will be available.

Outlier values will be evaluated for their validity; all data will be included unless judged to be invalid (e.g., deemed incompatible with life by Medical Monitor and/or deemed invalid by the DSMB).

Efforts will be undertaken at study sites to reduce the amount of missing data. Due to the severity of the condition and the short 90-day follow-up period, very little loss to follow-up is anticipated. For the primary efficacy endpoint, complete data will be used and missing data will not be imputed in the main analysis. Also, sensitivity analyses with missing data imputed by LOCF (Last Observation Carry Forward) and WCCF (Worst Case Carry Forward) methods will be undertaken to explore the effect of missing data on the endpoint and test the robustness of the estimate.

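### The SAP's next-visit rule can let an off-window mRS stand as the 90-day score for patients who withdraw after day 30, and the SAP does not say that a score or death observed at day 90 takes precedence

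*Supplement*

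**What the plan says.** SAP v2.0 section 10 (Premature Withdrawal and Missing Data) covers patients who withdraw before the day-90 assessment: "they are required to complete the withdrawal visit in the CRF". Three rules follow in the same section.

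1. A rule for clinic visit data, whether tabulated or analysed, reads: "this visit will be assigned to the next scheduled clinic visit for that subject, regardless of whether the date falls within". What is meant is the window of that later visit.
2. Withdrawn patients with at least one post-baseline measure of an endpoint are included in its analysis.
3. For the primary endpoint, "complete data will be used and missing data will not be imputed in the main analysis". LOCF and WCCF are sensitivity analyses only.

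The primary endpoint is the mRS at 90 (±7) days (Protocol V7.1 section 7.1, SAP section 3), analysed on all randomised patients (SAP section 7). The scheduled contacts are 36 hours, day 7 or discharge, day 30, day 90 and 12 months. mRS is collected from the day-7/discharge visit onward (Protocol V7.1 section 8.6).

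Protocol V7.1 section 9.5.3 says "The follow-up will continue even if the patient withdraws from the clinical trial", with an interview by telephone or in person at the scheduled visit time. Section 11.1 tells each patient that "he has the right to withdraw from this study at any time".

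**The concern.** For a patient who withdraws after the day-30 contact, rule 1 makes the withdrawal visit the day-90 visit, and rule 2 keeps that patient in the analysis. An mRS taken weeks early can then pass as an observed 90-day score. Under rule 3 alone, the same patient has a missing score. The SAP does not rank the rules, so two programmers could build different primary datasets from the same records.

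The early score can be wrong in either direction. A patient who is alive at withdrawal but dead by day 90 would be scored 5 or better instead of 6, and a survivor still recovering would be scored too badly. In an open-label trial, withdrawal may differ by arm and by clinical course. The common odds ratio and the mRS 0-2 and 0-3 proportions could then be biased, although the protocol provides for a contact at which the day-90 state might be learned.

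**Working it through.** **Which withdrawals reach the day-90 slot.** Withdrawals before the day-30 contact map to 36 hours, day 7/discharge or day 30. Only those between the day-30 and day-90 contacts map to day 90. The documents do not split withdrawals by time or arm. If all of the planned 10% attrition were withdrawal, that would be 0.10 × 502 = 50 patients. One third of them leaving after day 30 is 17, and two thirds is 33.

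**The plan's own figure.** Inputs from SAP section 6: control mRS 0-6 of 3, 4, 10, 17, 16, 12 and 38%; common OR 1.73; two-sided alpha 0.046; power 0.90; 1:1 allocation. The proportional-odds formula is N = 12(z_α + z_β)² / [(ln OR)²(1 − Σp̄³)]. OR 1.73 gives an EVT distribution of 5.1, 6.4, 14.6, 21.0, 16.3, 10.5 and 26.2%, so Σp̄³ = 0.0475. Then N = 12 × (1.995 + 1.282)² / (0.3004 × 0.9525) = 450.3, or 451 against 452 stated. With attrition, 452/0.9 = 502.2 against 502 stated. The sample size reproduces and is not in question.

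**Reference power.** V = N(1 − Σp̄³)/12 = 502 × 0.9525/12 = 39.8, and power = Φ(ln OR × √V − 1.995). With ln 1.73 = 0.548, this is Φ(0.548 × 6.31 − 1.995) = 92.8% with all 502 scores observed.

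**Equal substitution in both arms.** Assume the substituted scores carry no treatment effect and no deaths, because the patient is alive at the withdrawal visit. Refitting the proportional-odds model to the expected tables gives:
- 1% substituted: OR 1.72, power 92.4%
- 5%: OR 1.69, power 90.4%
- 10%: OR 1.64, power 87.5%

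**Selective substitution.** Assume a share of each arm withdraws at mRS 5 and dies before day 90, so that share moves from category 6 to category 5. For 10% BMM and 2% EVT under the null, categories 5 and 6 become 22% and 28% in BMM, and 14% and 36% in EVT. The model is refitted, and two-sided rejection at 0.046 is computed from V as above (both tails):

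| BMM / EVT share | Null OR (rejection) | OR 1.73 becomes (power) |
|---|---|---|
| none | 1.00 (4.6%) | 1.73 (92.8%) |
| 2% / 1% | 0.98 (4.7%) | 1.71 (92%) |
| 2% / 0% | 0.97 (5.0%) | 1.69 (91%) |
| 4% / 1% | 0.95 (5.6%) | 1.67 (90%) |
| 10% / 2% | 0.88 (11.8%) | 1.58 (82%) |
| 2% / 10% | 1.14 (11.8%) | 1.97 (99%) |

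The 10% rows are extreme. They need 0.10 × 251 = 25 patients of one arm to withdraw after day 30 and die by day 90. In BMM that is 25 of 0.38 × 251 = 95 expected deaths, or 26%. All withdrawal rates here are assumptions.

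**The case against.** The strongest reply is that the SAP does not clearly order the substitution. The next-visit rule is limited to clinic visit data, and Protocol V7.1 section 3.3 lists day 90 as a telephone visit. The later sentence written for the primary endpoint calls for complete data without imputation. On that reading, the next-visit rule serves by-visit tables and the specific sentence governs the main analysis. This has force: a reader might infer that the SAP definitely enters the early mRS in the main analysis, and the text does not settle that. But section 8.4 also allows day 90 in person, the next-visit rule covers analysis as well as summaries, and it is framed by withdrawal before the day-90 assessment. The conflict is real even if one reading is likelier.

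Other inferences go further than the documents:

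- Not every withdrawn patient is affected; earlier withdrawals do not map to day 90.
- Section 9.5.3 does not guarantee a true 90-day score. The sentence stands in a paragraph where "the investigator should follow up the outcome of any AEs", it names neither mRS nor vital status, and contact after withdrawal is not assured.
- The withdrawal visit may yield no mRS at all. It is absent from the schedule in section 8.6, and section 8.5 requires mRS at an unscheduled visit only for a neurological change.
- A patient who gives the day-90 interview has arguably completed that assessment and falls outside the rule, so two competing 90-day scores are possible but not established.
- Mortality is not directly distorted. SAP section 13 uses a Cox model on death times, which visit mapping does not move. What is unstated is only whether deaths after withdrawal are used.
- The per-protocol criterion "Follow-up interval exceeds the required time window" is no contradiction. Keeping such data in the FAS and excluding them from the PPS is the ordinary purpose of two sets.

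**Conclusion.** The point holds in a limited form. SAP section 10 contains a stated rule that, followed as written, allows an off-window mRS to be analysed as the 90-day score for patients who withdraw between the day-30 and day-90 contacts. It conflicts with the ±7-day window and with the no-imputation sentence, and nothing says that a day-90 mRS or death learned after withdrawal is used or ranks first.

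With the very little loss to follow-up that the SAP anticipates, the effect is small: OR 1.73 becomes about 1.69 to 1.71 if 2% of BMM and 0-1% of EVT patients withdraw at mRS 5 and then die, and null rejection stays at or below about 5%. Even 10% substituted equally in both arms costs about 5 power points (92.8% to 87.5%) under the no-effect, no-death assumption. Serious error needs substantial differential withdrawal: at an assumed 10% versus 2%, the null OR is about 0.88 or 1.14, depending on the arm, with rejection near 12%. No stated figure in the plan is wrong. The change is worth making because it is cheap and removes an ambiguity in the primary dataset.

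**What to change.** In SAP section 10:

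- Exclude the 90-day mRS endpoints (ordinal, 0-2, 0-3) from the next-visit rule, and report withdrawal-visit data at their actual date.
- State that an mRS observed at day 83-97, or a death by day 90, is used as randomised in the FAS, including after withdrawal where the patient has not refused contact.
- State that the score is otherwise missing in the main analysis and is handled by the planned LOCF and WCCF sensitivity analyses.

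In Protocol section 9.5.3, state that mRS and vital status are collected at the contacts after withdrawal unless the patient refuses further contact. Record the type of withdrawal on the CRF.

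The cost is SAP and protocol wording and one CRF field. No patients or visits are added, since section 9.5.3 already provides for the contacts.

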## **10. Statistical Analysis**

### **10.1 Sample size estimation**

In this study, a multicenter, open, randomized, parallel control design method will be used. The primary measure of efficacy will be the mRS score at 90 days ( $\pm 7$  days) after enrollment

(considered as ordered variable). According to the literature data and clinical expert opinions, the parameters were set as follows: (1) The proportion of mRS score 0-6 in control group will be 3%, 4%, 10%, 17%, 16%, 12% and 38%, respectively; (2) The average treatment effect of EVT improves the outcome with the common OR value for improvement of mRS reaching 1.74; (3) Two Interim analysis are considered. The adjusted level  $\alpha$  is 0.050 and power  $1-\beta$  is 0.90. (4) The randomization will be allocated to the intervention and the control group in a 1:1 ratio. Based on these parameters, the sample size will be 219 in each group. Considering a 10% attrition rate, the final total sample size will be 488 patients, with 244 patients in each group.

Interim analysis will take place when 1/2 (244) and 3/4 (366) of patients will have completed 3-month follow-up.” The corresponding significance levels based on the O’Brien & Fleming boundary are 0.003 (stage 1), 0.018 (stage 2) and 0.044 (stage 3, final analysis).

The PASS software (NCSS, LLC, version 11) was used to calculate the sample size.

## **10.2 Data collection and entry**

Paper-based CRF and electronic data capture (EDC) system will be used for data collection and input. All the content required by the protocol in the system must be filled. The unfilled content should be explained, and the reason needs to be marked in the EDC system.

### **10.2.1 Paper-based CRF filled out by the investigator**

Site investigators should use black or blue-black recording pens to fill out the paper-based CRF neatly and clearly to ensure that the data is clear and readable. If the paper-based CRF information needs to be modified, it should not be altered or overwritten. The correct information should be written next to the original information, signed and dated by the person who modified it. The clinical research monitor (Clinical Research Associate, CRA) will review the completeness and accuracy of the CRF and guide the investigator to make necessary corrections and supplements.

### **10.2.2 Data entry to the EDC system by CRC**

After the paper-based CRF is completed, the Clinical research coordinator (CRC) will

input the content of the paper CRF into the EDC system.

### **10.2.3 Submission to the EDC system after the approval of the investigator**

The paper-based CRF will be submitted after the investigator has approved it. After the data is submitted, all data revisions and feedback are carried out through the EDC system. If the EDC system has submitted a form that needs to be modified, contact the CRA of this center. After the CRA opens the form, the investigator can guide the CRC to modify the data in EDC system.

### **10.2.4 Data monitoring and query by CRA via EDC**

### **10.2.5 Data exportation from the EDC system**

After the data from the EDC system is exported to the database, it will be proofread by the data administrator. Obvious errors will be corrected by the data administrator. Other errors or missing values will be filled in the data query form, and the query form will be sent to the participating center for solutions through email, express, telephone or WeChat.

The participating centers are responsible for correcting the data in the EDC system after verifying the original data and related information. Site investigators must answer these queries by verifying or modifying relevant information or data.

## **10.3 Statistical considerations**

This section is an overview of the statistical considerations. It provides the general specifications for the analysis of the data to be collected and presented in the CSR. A final Statistical Analysis Plan (SAP) will be issued prior to database lockdown and before code breaking. The SAP will define all “pre-specified, planned analyses.”

All programming will be performed using SAS Version 9.4.

### **10.3.1 Analysis sets**

#### **(1) Full Analysis Set (FAS):**

Based on the principles of the Intent-to-Treat (ITT) analysis, all randomized subjects, either treated with medication or with EVT will be included in the FAS. The primary efficacy endpoint analysis of this study will be performed on the FAS.

## **(2) Per Protocol Set (PPS)**

The PPS is a subset that includes all subjects who were treated with the treatment assignment to which they were randomized and there are no clinically meaningful deviations from the protocol. Severe deviations from the protocol will be defined during the data auditing process, including but not limited to the following:

- 1) The subject is not in line with the inclusion criteria.
- 2) There are other treatments that potentially confound the appraisal of efficacy of the planned treatment.
- 3) Poor compliance.
- 4) Follow-up interval exceeds the required time window.

Secondary analysis will be conducted on the PPS. If its result are not consistent with that of the FAS, a detailed analysis to examine the difference(s) will be required.

## **(3) Safety Analysis Set (SAS)**

The SAS consists of all subjects who received treatment with at least one evaluation of the safety outcome.

### **10.3.2 Statistical considerations**

#### **(1) Baseline characteristics comparisons**

T-test or Wilcoxon rank sum test will be used for comparison between continuous variables, and Chi-squared tests, Fisher's exact test or Wilcoxon sum rank test will be used for comparison between categorical variables.

#### **(2) Efficacy Analysis**

Primary efficacy endpoint: Based on an ITT basis, an ordinal logistic regression model is used to calculate the common odds ratio between the two treatment groups. All statistics will be two-sided with  $p < 0.05$  considered significant.

Secondary Efficacy Analyses: Endpoints including the 90-day mRS 0-2 will be analyzed using a binary logistic regression model. The infarct core volume change from baseline will be analyzed using student t-test or Wilcoxon rank sum test as appropriate.

### **(3) Safety Analysis**

Safety events in the two treatment groups will be described based on the SAS dataset. Logistic regression will be used to compare the differences in safety endpoints such as intracranial bleeding events between the two groups. Chi-square test and Fisher's exact test will be used to compare the differences in the incidence of AEs and SAEs between the two groups.

### **(4) Subgroup analysis**

The mRS at 90 days will be presented for each level of the covariates listed below:

- (1) Age ( $< 70$  years vs.  $\geq 70$  years)
- (2) Last known well to randomization time ( $< 6$  h vs.  $\geq 6$  h)
- (3) Stroke severity before randomization (NIHSS $<16$  vs. NIHSS $\geq 16$  points)
- (4) IV thrombolysis or not
- (5) Occlusion site (intracranial ICA vs. M1 segment)
- (6) ASPECTS ( $< 3$  points vs.  $\geq 3$  points)
- (7) Infarct core volume ( $< 70$ ml vs.  $\geq 70$ ml)
- (8) Etiological subtype of stroke (cardiac embolism vs. large artery atherosclerosis)

### **10.4 Interim analysis**

Interim analysis will take place when 1/2 (244 cases) and 3/4 (366 cases) have completed 3-month follow-up. The O'Brien-Fleming boundaries will be used at the interim analysis as follows:

There are no established techniques for the assessment of interim trial efficacy boundaries using an ordinal logistic regression model (proportional odds model). Instead, we will revert to a simple dichotomous analysis of the mRS score at 0-2 defined at 90 days from randomization. The Z-statistic for this analysis shall be derived from the normal approximation of the binomial distribution as an unadjusted two-sample test of proportions. For a RCT comparing two treatment groups with respect to a binary outcome and two interim analysis, corresponding significance levels based on the O'Brien & Fleming boundary are 0.003 (stage 1), 0.018 (stage 2) and 0.044 (stage 3, final analysis).

With the result of the interim analysis, the DSMB will make the decision to continue or halt the study according to the test boundaries. The study will stop prematurely for futility if the result from the interim analysis indicate that an effective conclusion with the current sample size can't be achieved. Premature stopping for early success will be achieved if the interim analysis result proves the effect of the intervention arm at significance level. Otherwise, the study will be continued until the predefined termination date. In interim analysis, the final sample size can be adjusted if the estimation of the primary outcome is drastically different from the actual data.

